**Fig. 1 Fig1:**
[figure not shown]
Example template of recommended content for the schedule of enrolment, interventions, and assessments

##### Study day 1 (all eligible patients)

Eligible patients are required to check into the clinical site before surgery (day 0). The following procedures are performed at check-in: 1) review inclusion/exclusion criteria; 2) randomization; 3) review of concomitant medications; and 4) review of adverse events (AEs).

Additional laboratory tests are requested as required by the investigator.

All eligible patients are hospitalized and randomized into the two treatment groups: Group 1—intramuscular Naldebain^®^ (150 mg nalbuphine sebacate) 24 ± 12 h before surgery; Group 2—Intravenous PCA with fentanyl through 48 h postsurgery.

For pain assessment, patients in Groups 1 and 2 rate their pain intensity using the VAS pain scale prior to dosing or at day 1, respectively.

Vital signs are checked prior to dosing and once daily until day 6.

Group 1 receives Naldebain^®^, and the injection site is evaluated within 1 h prior to dosing.

##### Study day 0 to 5

All patients are given general anesthesia prior to their scheduled surgical procedure. If patients require additional medication for the treatment of pain, ketorolac and morphine can be used as supplemental analgesics as required. Post-surgery, the following evaluations are performed: 1) for pain assessment, all patients rate their average pain intensity using a VAS pain scale (assessments are performed before the first use of PCA or supplemental analgesics and then at 4 ± 1, 24 ± 2, 32 ± 3, and 48 ± 4 h, and once daily on day 3 to day 5 following surgery); 2) BPI evaluation is performed on day 2; 3) vital signs (temperature, respiratory rate, blood pressure, and heart rate) are examined once daily prior to the final visit; 4) in Group 1 (the IM-Naldebain^®^ group), the injection site is evaluated once daily until the final visit; 5) a review of concomitant medication and adverse events are record; and 6) in Group 2 (the IV-PCA group), the amount of fentanyl used is recorded from day 0 through day 2.

##### Study day 6

The following evaluations are performed at day 6: 1) for pain assessment, patients rate their pain intensity in the patient diary; 2) BPI is evaluated; 3) vital signs (temperature, respiratory rate, blood pressure and heart rate) are examined; 4) the injection site is evaluated; 5) a review of the AE record; and 6) a review of concomitant medication.

##### Final visit (discharge, day 6–30)

For safety concerns, the study will follow-up each patient until discharge (within a time window for discharge of 6–30 days). The patients will be evaluated for: 1) vital sign (temperature, respiratory rate, blood pressure, and heart rate) examination; 2) injection site evaluation; 3) laboratory tests, including hematological and biochemical tests, and urinalysis; 4) patient satisfaction (at the final visit, each patient is asked the following question (Table 2): “How satisfied were you with your postsurgical analgesia?” and patients are asked to classify themselves as either “highly satisfied,” “satisfied,” “uncertain,” “dissatisfied,” or “very dissatisfied”); 5) physical examination; 6) review of the AE record; and 7) review of concomitant medication.

**Table 2 Tab2:** Five-point rating of patient satisfaction

Rating	Description
1	Highly satisfied
2	Satisfied
3	Uncertain
4	Dissatisfied
5	Very dissatisfied

#### Patient background

The following items are investigated at the screening visit and the results are recorded on the CRF for the patient background data: informed consent, demographic information, vital signs, medical history, physical examination, 12-lead ECG, chest x-ray, and laboratory testing (complete blood count with differential, platelets, biochemical tests, and urinalysis).

#### VAS and patient diary

The VAS is a 10-cm numeric scale (0 = no pain to 10 = worst pain ever).

#### Short-form BPI

The short-form BPI is a self-reported scale that measures the severity of pain based on average pain (severity scores 0 = no pain to 10 = most severe pain). BPI is evaluated at days −1, 2, and 6.

#### Injection site evaluation (Table 3)

The injection site reaction is evaluated prior to dosing and once daily from day 1 to the final visit. A five-point rating is used (0 = no reaction, 1 = no swelling or erythema present, 2 = erythema at the site, no swelling is present, 3 = erythema and swelling present at the site, no treatment required, 4 = erythema and swelling present, treatment is required).

**Table 3 Tab3:** Five-point rating grade when assessing the injection site

Grade	Definition
0	No reaction
1	Burning/stinging or pain at the site of injection; no swelling or erythema present
2	Erythema at the site; no swelling present
3	Erythema and swelling present at the site; no treatment required
4	Erythema and swelling present; treatment required

#### Adverse events

An AE is any untoward medical occurrence in a patient administered the study drug that does not necessarily have a causal relationship with the treatment. An AE can be any unfavorable and unintended sign, symptom, or disease temporally associated with the use of the study drug, regardless of whether it is considered to be related to the study drug. This includes any newly occurring event or previous condition that has increased in intensity or frequency since the administration of the study drug. Lack of efficacy before the study end is not considered an AE.

A serious AE (SAE) is defined as an AE that meets any of the following criteria (Table 4): 1) results in death; 2) is life threatening; 3) results in inpatient hospitalization or prolongation of existing hospitalization; 4) results in a persistent or significant disability/incapacity; 5) results in congenital anomaly/birth defect; and 6) an important medical event.

**Table 4 Tab4:** Severity categories of adverse events

Severity	Description
Mild	Event may be noticeable to patient; does not influence daily activities; usually does not require intervention
Moderate	Event may be of sufficient severity to make patient uncomfortable; performance of daily activities may be influenced; intervention may be required
Severe	Event may cause severe discomfort; usually interferes with daily activities; patient may not be able to continue in the study; treatment or other intervention usually required
Serious	Results in death or life-threatening situation; inpatient hospitalization or prolongation of existing hospitalization; persistent or significant disability/incapacity; or congenital anomaly/birth defect or important medical event

The investigator evaluates the intensity of each AE using the following definitions (Table 4):

Mild—event may be noticeable to the patient; does not influence daily activities; usually does not require intervention.

Moderate—event may be of sufficient severity to make patient uncomfortable; performance of daily activities may be influenced; intervention may be required.

Severe—event may cause severe discomfort; usually interferes with daily activities; patient may not be able to continue in the study; treatment or other intervention usually required.

After careful consideration, the investigator evaluates the relationship of each AE to the study drug by applying the following definitions (Table 5):

**Table 5 Tab5:** Determining the relationship between adverse events and the study drug

Relationship	Description
Certain	An adverse event, including laboratory test abnormality, occurring in a plausible time relationship to drug administration, which cannot be explained by concurrent disease or other drugs or chemicals
Probable/likely	An adverse event, including laboratory test abnormality, with a reasonable time sequence to administration of the drug that is unlikely to be attributed to a plausible response on withdrawal
Possible	An adverse event, including laboratory test abnormality, with a reasonable time sequence to administration of the drug, which could also be explained by concurrent disease or other drugs or chemicals. Information on drug withdrawal may be lacking or unclear
Unlikely	An adverse event, including laboratory test abnormality, with a temporal relationship to drug administration which makes a causal relationship improbable, in which other drugs, chemicals, or underlying disease provide plausible explanations
Not related	An adverse event which is judged to be clearly due to extraneous causes (e.g., disease and environment)

Certain—an AE, including laboratory test abnormality, occurring in a plausible time relationship to drug administration, which cannot be explained by concurrent disease or other drugs or chemicals. Response to withdrawal of the drug (de-challenge) should be clinically plausible. The event must be definitive pharmacologically or phenomenologically, using a satisfactory re-challenge procedure if necessary.

Probable/likely—an AE, including laboratory test abnormality, with a reasonable time sequence to administration of the drug that is unlikely to be attributed to a plausible response on withdrawal. Re-challenge information is not required to fulfill this definition.

Possible—an AE, including laboratory test abnormality, with a reasonable time sequence to administration of the drug, but which could also be explained by concurrent disease or other drugs or chemicals. Information on drug withdrawal may be lacking or unclear.

Unlikely—an AE, including laboratory test abnormality, with a temporal relationship to administration of the drug which makes a causal relationship improbable, and in which other drugs, chemicals, or underlying disease provide plausible explanations.

Not related—an AE that is judged to be clearly due to extraneous causes (e.g., disease and environment).

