#### Safety analysis

For the safety analysis, continuous variables will be tested using a *t* test and categorical variables will be compared by chi-square or Fisher’s exact test. The coding system used will be the Medical Dictionary for Regulatory Activities (MedDRA).

AEs will be summarized descriptively according to body system, MedDRA preferred term, center, treatment, and overall outcome. If more than one type of event occurs within a system organ class/preferred term for the subject, the subject is counted only once when summarizing the data by system organ class/preferred term. Incidence tables of intensity, drug relationship, drug-related AE (including certain, probable, and possible), action taken regarding the study drug, and whether treatment was required for an event or SAE will be presented by center, treatment, and overall outcome. Incidence rates ≧2%, ≧10%, and rates for Naldebain^®^ greater than two times PCA fentanyl will be presented.

In terms of severity and relationship summaries, the most severe event and the most directly related event will be presented in summary tables in the case of multiple occurrences per subject. Only treatment-emergent events will be included in the AE summary; other events will only be listed. Treatment-emergent events include events that start on or after the first day of study drug administration, that were not present at baseline, or were present at baseline but increased in severity after the start of study drug administration.

A frequency table of injection site will be presented according to center, time, and treatment. Descriptive statistics of recovery duration (hours, defined as from first score 0 over second score 0 or 1) for injection site assessment will be presented according to center and treatment.

Incidence of SAEs will be tabulated. SAE incidents will be summarized descriptively according to center, system organ class, preferred term, treatment group, and overall outcome.

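### The Probable/likely causality grade has its withdrawal clause reversed and no alternative-cause condition, and Table 5 shortens Certain, so the AE table by relationship may misclassify events

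*Protocol article*

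**What the plan says.** The Adverse events section instructs the investigator to grade the relationship of each AE to study drug using the definitions in Table 5, which are then repeated, in places more fully, in the text.

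- **Probable/likely** is worded the same in both places: an event "with a reasonable time sequence to administration of the drug that is unlikely to be attributed to a plausible response on withdrawal". The text adds only "Re-challenge information is not required to fulfill this definition".
- **Certain** shares one condition in both places, that it is an event "which cannot be explained by concurrent disease or other drugs or chemicals". The text then adds two more: "Response to withdrawal of the drug (de-challenge) should be clinically plausible" and "The event must be definitive pharmacologically or phenomenologically, using a satisfactory re-challenge procedure if necessary". Table 5 has neither.
- **Possible** covers an event "which could also be explained by concurrent disease or other drugs or chemicals".
- **Unlikely** needs a temporal relationship "which makes a causal relationship improbable, and in which other drugs, chemicals, or underlying disease provide plausible explanations".
- **Not related** is for events judged clearly due to an extraneous cause.

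The Safety analysis section tabulates relationship by treatment, shows each subject's most strongly related event, and pools three grades as "drug-related AE (including certain, probable, and possible".

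**The concern.** The two top grades treat the same evidence in opposite ways. Under Certain, a plausible response to stopping the drug supports causality. Under Probable/likely, taken as written, an event attributable to such a response does not qualify. Probable/likely also lacks any condition on concurrent disease or other drugs, although every other grade addresses alternative or extraneous causes in some form. The missing condition is what should separate Probable from Possible.

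The text's Certain is narrower than Table 5's, and the instruction to investigators points to the table.

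What is at stake is the table of AEs by relationship. Where an event satisfies two grades or none, its place depends on which clause the investigator follows. The arms also differ in what can be observed. Naldebain is one intramuscular dose (Study drug administration) that the Discussion says takes about 6 days to be released fully, while the PCA machine may be removed before 48 h (Overall design). A rule that turns on withdrawal may therefore work differently in the two arms.

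**Working it through.** The plan gives no figure on this point, so there is none to reproduce. The check sets the definitions side by side and then applies them literally.

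**Step 1. Clauses compared**

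| Grade | Timing | Other causes | Withdrawal | Definitive event |
|---|---|---|---|---|
| Certain, text | plausible | excluded | plausible response expected | required |
| Certain, Table 5 | plausible | excluded | not mentioned | not mentioned |
| Probable/likely, both | reasonable | not mentioned | plausible response counts against | not mentioned |
| Possible, both | reasonable | could explain the event | information may be absent | not mentioned |
| Unlikely, both | makes causality improbable | offer an explanation | not mentioned | not mentioned |
| Not related, both | not mentioned | clearly the cause | not mentioned | not mentioned |

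**Step 2. Profiles.** Take events with reasonable timing and cross other cause (none / could explain), withdrawal response (plausible / not plausible / not assessable) and definitive event (yes / no): 2 × 3 × 2 = 12. Reasonable timing rules out Unlikely. No profile has an event clearly due to something else, so Not related is not used.

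A coding assumption is needed for a response that is not assessable. First take it as meeting Probable's clause (there is no withdrawal response to attribute the event to) and failing the text's Certain.

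- Certain by the text: 1 × 1 × 1 = 1. Certain by Table 5: 1 × 3 × 2 = 6. They differ on 6 − 1 = 5.
- Probable as written: 2 × 2 × 2 = 8.
- Possible: 1 × 3 × 2 = 6.
- Both Probable and Possible: 1 × 2 × 2 = 4.
- No grade under the text: 12 − (1 + 8 + 6 − 4) = 1. This is the event with no other explanation, a plausible response to withdrawal and no definitive mechanism. Table 5 would call it Certain.

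**Step 3. Sensitivity to the coding**

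| Not assessable is read as | Probable and Possible | No grade (text) | Certain differs, Table 5 against text |
|---|---|---|---|
| meeting Probable, failing Certain | 4 | 1 | 5 of 6 |
| meeting both | 4 | 12 − (2 + 8 + 6 − 1 − 4) = 1 | 4 of 6 |
| failing both | 2 | 12 − (1 + 4 + 6 − 2) = 3 | 5 of 6 |

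Under the first two readings the ungraded profile needs an observed withdrawal response, which points to PCA. Under the third, two of the three ungraded profiles are not assessable, which points to the injection. The direction of any arm effect therefore depends on a reading that the protocol does not settle.

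**Step 4. Finer scale.** Adding a middle level for other cause (unlikely) gives 3 × 3 × 2 = 18 profiles. With the first coding, the overlap of Probable and Possible stays at 4. Three profiles fit no grade under the text and two under Table 5.

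**Step 5. Which tables are reached.** Every profile that fits a grade falls in Certain, Probable or Possible, and the drug-related table pools all three. Misgrading among them alters the by-relationship table but not the pooled one. Only a profile with no grade can alter the pooled table.

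**The case against.** The strongest reply is that little follows in practice. Several parts of it stand.

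- **Pooling.** Because the drug-related table combines the three affected grades, the overlaps stay inside it. A reader might infer that the drug-related comparison is itself distorted; the documents do not support that beyond events that fit no grade. Nor do they say that an ungraded event is counted as unrelated: it fails Unlikely and Not related as well.
- **Not related exists.** A reader might infer that any well-timed Naldebain event must qualify as Probable even with an evident other cause. An event clearly due to something else belongs in Not related, and reading an unobservable withdrawal as meeting the clause is an assumption that the protocol does not make.
- **Table 5 is an abbreviation.** The shared sentence on Certain is the same and the text adds to it. This is an omission, not two opposing rules.
- **Rarity.** All patients have general anesthesia and surgery and may receive ketorolac or morphine, so many events could have another explanation and would be at least Possible.
- **Judgement.** Investigators record an opinion and may follow the evident intent.

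The reply does not remove the defect. The clause could be read as excluding withdrawal symptoms, but Probable would still lack an alternative-cause condition. Possible tolerates missing withdrawal information, yet still requires another potential explanation, so it does not take in the ungraded event. The same wording appears in both Table 5 and the text, so it is not an effect of shortening the table.

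**Conclusion.** The point holds as a minor but operative error of definition. Probable/likely runs against the protocol's own rule for Certain and omits the condition on other causes, and Table 5's Certain is incomplete. Read literally, Probable and Possible overlap, and one kind of event has no grade under the text. The table by relationship may misclassify events and cannot be reproduced from the definitions alone.

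A difference between arms is a reasonable inference from what can be observed in each. It is no more than that, since neither size nor direction can be derived. The profile counts rest on the stated codings and say nothing about how often such events occur.

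The safety endpoints (TEAE incidence and percentage of abnormality in vital signs, laboratory tests and injection site) do not use causality. They, the primary endpoint and the sample size are unaffected.

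**What to change.** 1. Reword Probable/likely, in Table 5 and the text alike, to require a reasonable time sequence, an event unlikely to be due to concurrent disease or other drugs and, where the drug was stopped, a plausible response to stopping.
2. Give Certain in Table 5 the same conditions as in the text.
3. State that withdrawal response is not applicable to the single injection, for all grades.
4. Have investigators re-confirm grades already assigned, preferably before the by-arm tables are produced.

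Applied to the 12 profiles, items 1 to 3 bring the overlap of Probable and Possible from 4 to 0 and give the ungraded event a grade. They leave 2 profiles without one: no other cause, drug stopped, no plausible response, definitive or not (1 × 1 × 2). One further sentence should say where these go, and that the highest grade fully met applies, since Certain then lies within Probable.

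The cost is the wording of two definitions and of the CRF completion guidance, plus the re-confirmation. Trial status reports 20 patients enrolled by the end of January 2018 and completion expected in December 2018, so many grades may already exist. Treatment, endpoints and sample size do not change.

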#### Adverse event reporting

All AEs, regardless of causality, that occur between the time the study medication is administered and completion of the treatment phase are reported. Those meeting the definition of SAEs are reported using the SAE form.

All AEs, regardless of seriousness, severity, or presumed relationship to the study drug, are recorded using medical terminology in the source document and the CRF. Whenever possible, diagnoses are given when signs and symptoms are due to a common etiology (e.g., cough, runny nose, sneezing, sore throat, and head congestion should be reported as “upper respiratory infection”). Investigators must record in the CRF their opinion concerning the relationship of the AE to study therapy. All measures required for AE management must be recorded in the source document and according to sponsor instructions.

The investigator must report all such events to the appropriate independent ethics committee (IEC)/institution review board (IRB) that approved the protocol unless otherwise required and documented by the IEC/IRB.

#### Serious adverse events

Information regarding SAEs is transmitted to the sponsor using the SAE form, which must be signed by a member of the investigational staff.

All SAEs that have not been resolved by the end of the study, or that have not resolved upon discontinuation of the patient’s participation in the study, must be followed up until any of the following occurs: 1) the event resolves; 2) the event stabilizes; 3) the event returns to baseline, if a baseline value is available; 4) the event can be attributed to agents other than the study drug or to factors unrelated to study conduct; and 5) when it becomes unlikely that any additional information can be obtained (patient or healthcare practitioner refusal to provide additional information, lost to follow-up after demonstration of due diligence with follow-up efforts).

The death of a patient in a clinical study, regardless of whether the event is exempted from association with the investigational agent, is considered an SAE.

### Data management and statistical methods

#### Study endpoints

The following endpoints will be evaluated.

The primary efficacy endpoint is the pain assessment (time-specific pain intensity) calculated as the AUC of VAS pain intensity scores through 48 h postsurgery.

The secondary efficacy endpoints are as follows: 1) the total consumption (mg) of supplemental analgesics administered postsurgery; 2) pain assessment calculated as the AUC of VAS pain intensity scores from the end of surgery through day 6; 3) pain intensity and interference of BPI; 4) patient satisfaction on a five-point rating (Table 2); and 5) length of postoperative hospital stay.

The safety endpoints are as follows: 1) incidence of TEAE; and 2) percentage of abnormality from baseline to final visit in vital signs, laboratory tests, and injection site evaluations.

